## Abstract

**Background:**

For cases of severe traumatic brain injury, during primary operation, neurosurgeons usually face a dilemma of whether or not to remove the bone flap after mass lesion evacuation. Decompressive craniectomy, which involves expansion of fixed cranial cavity, is used to treat intra-operative brain swelling and post-operative malignant intracranial hypertension. However, due to indefinite indication, the decision to perform this procedure heavily relies on personal experiences. In addition, decompressive craniectomy is associated with various complications, and the procedure lacks strong evidence of better outcomes. In the present study, we designed a prospective, randomized, controlled trial to clarify the effect of decompressive craniectomy in severe traumatic brain injury patients with mass lesions.

**Methods:**

PRECIS is a prospective, randomized, assessor-blind, single center clinical trial. In this trial, 336 patients with traumatic mass lesions will be randomly allocated to a therapeutic decompressive craniectomy group or a prophylactic decompressive craniectomy group. In the therapeutic decompressive craniectomy group, the bone flap will be removed or replaced depending on the emergence of brain swelling. In the prophylactic decompressive craniectomy group, the bone flap will be removed after mass lesion evacuation. A stepwise management of intracranial pressure will be provided according to the Brain Trauma Foundation guidelines. Salvage decompressive craniectomy will be performed for craniotomy patients once there is evidence of imaging deterioration and post-operative malignant intracranial hypertension. Participants will be assessed at 1, 6 and 12 months after randomization. The primary endpoint is favorable outcome according to the Extended Glasgow Outcome Score (5–8) at 12 months. The secondary endpoints include quality of life measured by EQ-5D, mortality, complications, intracranial pressure and cerebral perfusion pressure control and incidence of salvage craniectomy in craniotomy patients at each investigation time point.

**Discussion:**

This study will provide evidence to optimize primary decompressive craniectomy application and assess outcomes and risks for mass lesions in severe traumatic brain injury.

**Trial registration:**

ISRCTN20139421

## Background

Severe traumatic brain injury (STBI) is a major cause of death in young adults in developed countries [1]. In China, due to increasing traffic accidents, head injury occurs above 1 per 1000 [2]. The mortality of STBI is between 30 % and 50 %. According to a report from the Asian Development Bank, the annual economic loss from traffic accidents is equivalent to 1 %–3 % of China’s gross national product [3]. Considering the per capita income and limited medical resources, rational and effective treatment of STBI is of important economic and social significance.

Most STBI patients with intracranial hypertension attribute to mass lesions, such as contusion and subdural haematoma (SDH) [4, 5]. Severe primary injury and exasperate condition necessitate emergent surgical intervention. The available type of operation is either craniotomy or decompressive craniectomy (DC).

Craniotomy is the most widely used surgical treatment for STBI. This operation keeps the skull intact but the risk of post-operative refractory hypertension remains; thus, requires a salvage surgery. DC is another broadly used operation for STBI rescue, which involves the removal of the frontal, parietal and temporal skull to expand fixed cranial cavity. Some studies indicated that DC could effectively alleviate refractory intracranial hypertension [6–10]. However, using DC to treat STBI has been controversial since the 1970s [11, 12]. The focus of debate resides in whether DC would be able to improve the prognosis of patients. Current guidelines only suggest performing set the role of DC as a ‘surgical choice’ [5, 13].

Some studies which suggesting primary DC proposed that early aggressive intervention could mitigate the secondary damages of increased intracranial cerebral pressure (ICP) [10, 14–18]. In Europe, a retrospective study of 729 patients revealed that one-third of patients with STBI who received emergency surgery still needed DC even after haematoma evacuation [4]. Others who regarded DC as a second-tier salvage surgery considered that the long-term, frustrating recovery increased the uncertainty of DC [19]. Moreover, the complications remain perplex to surgeons [20, 21]. From the early stage of hemorrhagic progression to the late of cerebrospinal fluid disturbances, all these pathophysiologic changes would negatively impact the outcome of treatment [21–23]. Some authors pointed out that DC rests on the purpose of life-saving but costs severe disability in return [24, 25].

Except for fulminant intra-operative swelling, when surgeons take the risk of post-operative refractory hypertension into account, the decision of surgical option heavily relies on personal experiences. Thus, with the resurgence of DC, demands for compelling evidence regarding the use of DC in clinical practice have gathered momentum.

There are a few randomized controlled trials that have studied the use of DC for STBI. The results from completed trials cannot be generalized for solving the above questions [26]. DECRA study enrolled 155 cases of traumatic diffusion injury and the results suggested that DC did not show superiority over the best medical treatments [8]. Some commentators pointed out that the high crossover of patients from medical group to DC group in the DECRA could influence the outcomes [27]. Another notable trial is the RESCUE-ICP, which has collected data from 400 cases [28]. RESCUE-ICP permits craniotomy for mass lesion evacuation but excludes primary DC using. The results of this study remain to be concluded. RESCUE-ASDH, an ongoing trial, projects to compare primary DC and craniotomy in STBI patients with mass lesions [29].

However, it is common that the brain swells beyond the border of the skull window after mass lesion evacuation. Randomizing patients with brain swelling to craniotomy would impair patient's benefit. In contrast, screening out these patients would decrease study validity because intra-operative brain swelling is exactly indication for DC. In our hospital, primary DC is only selected for fulminant brain swelling, which we call therapeutic DC. The prophase study demonstrated that 54 % of patients reached a favorable outcome at 12 months after receiving therapeutic DC [30]. Even for some patients with fixed and dilated pupils, the bone flap could still be replaced. We also found there might be some predictive values of initial ICP for the risk of post-operative refractory intracranial hypertension [31]. All of these results need careful interpretation and prospective study confirmation.

Thus, considering the above background, we designed a clinical trial named prospective, randomized evaluation of therapeutic decompressive craniectomy in severe traumatic brain injury with mass lesions (PRECIS).

## Methods

### Study design

PRECIS is a prospective, randomized, assessor-blinded, controlled clinical trial designed at the West China Hospital, Sichuan University (Fig. 1). The study process will follow the Declaration of Helsinki [32]. The ethical approval was granted for the protocol version 1.2 by the Biological and Medical Ethics Committee (BMEC) of West China Hospital (No. 2015-17). The trial has been registered in the Current Controlled Trials (ISRCTN20139421). Whereas the neurologic status of STBI patients who will not be expected to give consent themselves, the lineal consanguinity or legal surrogate will be fully informed of the study purpose, procedure, potential risks and benefits. Before the trial process begins, a triplicate consent will be signed by a kin or a surrogate. Patients have the right to withdraw any time during the trial.

**Fig. 1 Fig1:**
[figure not shown]
Flowchart of PRECIS outline

### The primary hypothesis

Therapeutic DC, which is performed on the basis of emergence of intra-operative brain swelling, results in a better outcome compared with prophylactic DC for STBI patients with mass lesions.

### The secondary hypothesis

Therapeutic DC results in fewer complications and a better quality of life compared with prophylactic DCThe risk of salvage craniectomy for post-operative refractory hypertension in primary craniotomy patients can be quantified by clinical features.

### Eligibility

#### Inclusion criteria

Between 15 and 65 years old;Glasgow Coma Scale (GCS) ≤ 8;Presence of high- or mix-density lesion ≥ 25 ml (contusion, intraparenchymal and SDH);Progressive deterioration of neurological status after 24 h of injury (GCS motor score decreases by 2 points or blunt pupillary response);

#### Exclusion criteria

Bilateral mydriasis of critically endangered status;Cerebellum contusion;Penetrating brain injury;Serious extracranial comorbidites with Abbreviated Injury Scale (AIS) > 3;Beyond 24 h after injury;Known mental or physical disability which would confound outcome assessment;Breastfeeding or pregnancy;Definite surgical contraindications;

### Interventions

To increase consistency between groups, most procedures are the same between the therapeutic DC group and the prophylactic DC group, except the bone flap management. Once the legal surrogate signs consent and confirms randomization, the intervention commences. Before the operation, the best medical treatments will be administered in accordance with the recommendation of the BTF guidelines [33]. For obtaining full course (initial, intra-operative and post-operative) of ICP and CPP variations, ICP monitor will be placed before the craniotomy and kept at least 5 days after surgery. Given the patients with mass lesion often associate with ventricles compression and midline shift, intraparenchymal ICP monitor will be preferred. The probe will be properly placed and fixed in the frontal lobe of lesion side drilling through the designed craniotomy incision without affecting normal procedure.

The unilateral trauma craniotomy model will be adopted, as suggested by Potts et al. [34]. The scalp flap should locate 1 cm beyond the border of the skull window. Craniotomy should reach at least 15 × 12 cm with fully exposed areas, which extended down to the temporal base and curve round the parietal to the side of the midline within 2 cm. After mass lesion evacuation, the dura should be sutured on relaxation and expansion by the temporal fascia or artificial dura. Then, for the prophylactic DC group, the bone flap will be removed. For the therapeutic DC group, the decision of whether or not to replace the bone flap will depend on brain swelling. If the brain tissue protrudes above the base of the temporal skull window, the bone flap will not be replaced.

General care monitoring is aimed to maintain SaO_2_ > 95 %, mean systolic blood pressure > 90 mmHg, temperature < 37 °C and PaCO_2_ 35-40 mmHg. Central venous catheters will be placed in all patients for volume monitoring and resuscitation.

As per the BTF guideline, a stepwise approach will be preferred to regulate ICP management. Maintaining ICP < 25 mmHg and CPP > 60 mmHg are the target of the critical care treatment. Conventional therapies include head elevation (30°), ventilation, sedation, osmotic dehydration, external ventricular drainage and neuromuscular blockade. The short active propofol (5–100 μg/kg/min) and fentanyl (25–100 μg/h) are used for sedation. Mannitol (1 g/kg) is routine diuretic for osmotherapy. Equiosmolar hypertonic saline (23.4 %, 0.686 ml/kg in bolus) will be considered in patients with refractory intracranial hypertension or rebound phenomenon treated by mannitol. The short half-life of vecuronium (0.2 mg/kg/h) is selected for neuromuscular paralysis agent. Hyperthermia (32 °C–34 °C) will be added to the STBI patients when ICP is refractory even maximal medical treatment.

During critical care, repeated computed tomography (CT) scan will assess intracranial evolution if ICP > 20 mmHg. For craniotomy patients, salvage DC will be performed when there are deterioration of imaging findings (midline shift > 5 mm and/or cisternal compression) and malignant intracranial hypertension (ICP 25–30 mmHg > 1 h or ICP > 30 mmHg, regardless time). For DC patients, even there is no consensus on the optimal time of cranioplasty [35], and systematic review also questioned the definition of “early” which varies from 1 to 4 months [36, 37], it is rational to recommend bone flap replacement as early as 2 months after surgery once their performances achieving the clinical standard.

Scheduled CT scan will be performed at 1, 3, 7, 30 and 180 days after surgery. Additional CT scan will carry out depending on the condition of patient.

### Follow-up and data collection

After randomization, patients will be assessed at 1 week and 1, 6 and 12 months. Patients who cannot be followed up at seven days will be assessed upon being discharged. For upfront exit patients, their surrogates should mark the previous data whether or not could be used in study. All patient information and imaging findings will be uploaded to a database using the case report form (CRF).

The initial data collection will be assessed at the emergency room by an attending physician. This collection will include baseline status, torso and/or extremities AIS, trauma severity (GCS, motor score and pupillary reaction), CT parameters (mass lesion type, volume of haematoma and midline-shift), time of injury-to-operation, cause of injury and initial laboratory features (arterial blood gas parameters, coagulation and platelet count).

The 1-week follow-up will include intra-operative brain swelling event, salvage craniectomy, laboratory features, early complications and ICP and CPP control. Intra-operative monitoring values will be recorded at the point of probe fixation, dura incision, dura suture and scalp closure. Post-operative ICP control will be recorded as daily ICP burden (number of hrs/d with ICP > 25 mmHg) and total ICP burden (number of days with ICP > 25 mmHg), as well as the same method recording daily and total CPP burden (CPP < 60 mmHg) [38].

At 1, 6 and 12 months follow-up, the independent blinded assessor will face-to-face evaluate intervention outcomes, quality of life, late complications and time of cranioplasty using standard questionnaire. The questionnaire includes the Extended Glasgow Outcome Score (GOSE), EQ-5D. If the discharged patients cannot attend scheduled follow-up, especially at time point of 6 or 12 months, the questionnaire will be sent to the documented permanent address. Only if these methods are invalid, the surrogate will be investigated to finish the questionnaire by telephone.

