### Outcomes

The Primary endpoint is a favorable outcome at 12 months after randomization as measured by GOSE (5–8). The core secondary endpoint is the quality of life indicated by EQ-5D. Further secondary endpoints include mortality and complications at corresponding time point, ICP and CPP control and incidence of salvage DC in craniotomy patients.

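### Total ICP and CPP burden are undivided day counts over monitoring time that varies between patients and ends at death, so a between-arm difference in control can be attenuated

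*Protocol article*

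**What the plan says.** All references are to the Protocol article.

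- **Definition of the totals** (Follow-up and data collection): "and total ICP burden (number of days with ICP" above 25 mmHg); for CPP, "as well as the same method recording daily and total CPP burden (CPP < 60 mmHg". Neither total has a denominator.
- **Companion measure** (same section): "daily ICP burden (number of hrs/d with ICP > 25 mmHg", which is already scaled to a day.
- **Length of monitoring** (Interventions): "ICP monitor will be placed before the craniotomy and kept at least 5 days after surgery". This is a minimum; no maximum and no common counting window is given.
- **When it is collected** (Follow-up and data collection): the 1-week follow-up covers "early complications and ICP and CPP control", among other items. "Patients who cannot be followed up at seven days will be assessed upon being discharged".
- **Role** (Outcomes): the further secondary endpoints include "ICP and CPP control and incidence of salvage DC in craniotomy patients".
- **Incomplete patients** (Statistical analysis): the worst-outcome rule names drop-outs and patients who depart from their allocation. It does not name death during monitoring. The secondary outcomes listed there for analysis are quality of life, mortality and complications; ICP and CPP burden are not listed.

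**The concern.** A count of bad days measures two things at once: how badly pressure was controlled, and how many days were available to be counted. The second differs between patients for reasons unrelated to control (probe kept 5 days or longer, discharge before day 7). It is also cut short by death, which may itself result from lost control. A patient with ICP above threshold throughout who dies on day 2 scores 2, below a survivor with three bad days.

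The arms differ in bone-flap management, and the Background section says that craniotomy leaves a risk of refractory post-operative hypertension. ICP control is therefore the secondary endpoint closest to the mechanism under test. If the arm with worse control also has more early ICP deaths, the total understates how much worse it is. Expressing the total in hours would not cure this, because hours are truncated in the same way.

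**Working it through.** The plan gives no figure for burden, so there is none to reproduce. Taken from the plan: the day-count definition, the 5-day minimum and the 1-week visit. Everything else below is an **assumption** chosen to show the mechanism.

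**Notation.** *W* = days monitored in survivors; *q* = share of a survivor's days above threshold; *m* = share of the arm dying early of raised ICP; *d* = days lived by those patients, all above threshold.

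**1. Monitoring length alone.** A survivor's expected count is *qW*. With *q* = 0.40: 0.40 × 5 = 2.0 and 0.40 × 7 = 2.8. The count is 40% higher with identical control.

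**2. Early death.**
- Mean raw count in an arm = (1 − *m*)*qW* + *md*.
- Mean per-patient share of monitored time above threshold = (1 − *m*)*q* + *m* × 1.

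With the same *q* in both arms, the raw counts differ by (*m*B − *m*A)(*d* − *qW*) and the shares by (*m*B − *m*A)(1 − *q*). The share always moves the right way. The raw count does so only when *d* > *qW*, that is, beyond 2.0 days for *W* = 5 and 2.8 days for *W* = 7.

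With *q* = 0.40, *m* = 10% in arm A and 30% in arm B (the worse arm):

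| W | d | Count A | Count B | B − A |
|---|---|---|---|---|
| 5 | 1 | 0.9×2.0 + 0.1×1 = 1.90 | 0.7×2.0 + 0.3×1 = 1.70 | −0.20 |
| 5 | 2 | 2.00 | 2.00 | 0 |
| 5 | 3 | 2.10 | 2.30 | +0.20 |
| 7 | 1 | 0.9×2.8 + 0.1×1 = 2.62 | 0.7×2.8 + 0.3×1 = 2.26 | −0.36 |
| 7 | 2 | 2.72 | 2.56 | −0.16 |
| 7 | 3 | 2.82 | 2.86 | +0.04 |

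The share is 0.9×0.40 + 0.1 = 0.46 in A and 0.7×0.40 + 0.3 = 0.58 in B in every row. The difference of 0.12 equals 0.12 × 5 = 0.60 days on a 5-day scale, against +0.20, 0 or −0.20 from the raw count.

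**3. A milder case.** Survivors at 1.5 of 5 days (*q* = 0.30), deaths on day 2, *m* = 15% v 5%. Raw: 0.85×1.5 + 0.15×2 = 1.575 v 0.95×1.5 + 0.05×2 = 1.525. Share: 0.85×0.30 + 0.15 = 0.405 v 0.95×0.30 + 0.05 = 0.335. The raw difference is 0.05 day, against 0.07 × 5 = 0.35 day on the share scale. The direction is right but the difference is one seventh of the size.

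**4. If survivors in the worse arm also have higher ICP.** *W* = 5, *d* = 1, *q* = 0.40 in A and 0.50 in B, *m* = 10% v 30%. Raw: 1.90 in A v 0.7×2.5 + 0.3×1 = 2.05 in B. Share: 0.46 v 0.7×0.50 + 0.3 = 0.65. The count again points the right way, with a difference of 0.15 day against 0.19 × 5 = 0.95 day.

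**The case against.** The definition stands in a data-collection section, no test of the total is stated, and windows and denominators are often left to an analysis plan that is not shown here. Daily burden is recorded beside the total, and mortality and salvage craniectomy are separate secondary endpoints, so excess early deaths would be visible to anyone who reads the results together. Collection at one week suggests a spread of only about 5 to 7 days in survivors.

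Much of this stands, and it limits the point to one of two recorded forms of a further secondary endpoint. It does not remove the point. The article does not leave the total open; it fixes it as an undivided count, and an analysis plan that divided by monitored time would be replacing that definition. A 5-to-7-day cap, which the article does not state as the counting window, would still leave the spread in step 1 and the truncation by death.

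Three stronger readings are tempting but unsupported:

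- *The worse arm will show an equal or lower total.* This needs ICP deaths early enough that days lived do not exceed a survivor's expected bad days. The article gives overall mortality of 30% to 50% for severe injury but no timing, and steps 3 and 4 show attenuation without reversal.
- *Probes stay longer in patients whose ICP is still high, biasing the arms.* The article does not say so, and nothing in it indicates that monitoring time differs between arms. The 2.0 v 2.8 contrast is between patients.
- *Death must be ranked worst.* That is one choice among several. It turns a pressure measure into a composite with mortality, which is already an endpoint.

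**Conclusion.** The point holds as a weakness in a stated definition. Total ICP and CPP burden depend on how long a patient was monitored and whether the patient lived, as well as on control. Under the assumptions shown, equal control gives totals 40% apart between 5 and 7 monitored days. A true difference between arms is attenuated, for example 0.05 day where the share implies 0.35. With 30% v 10% early ICP deaths and 40% bad days in survivors over 5 days, it is masked for deaths on day 2 (2.00 v 2.00) and reversed for day 1 (1.70 v 1.90), but not for day 3 (2.30 v 2.10). Death rates, timing and daily shares are all assumed, so these figures show what can happen and do not forecast it. Daily burden in hours per day, the primary GOSE endpoint and the sample size are not affected. The definition should be changed, but the trial's main conclusion does not rest on it.

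**What to change.** For the between-arm comparison, define total ICP burden and total CPP burden over one common window, the first 5 post-operative days, as time beyond threshold divided by time monitored.

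- Form the ratio per patient and then compare arms. Pooling days across patients gives early deaths little weight: in the first table row it yields 1.90/4.6 = 0.413 v 1.70/3.8 = 0.447, against 0.46 v 0.58 per patient.
- Report monitored time and deaths within the window by arm beside the comparison.
- Treat readings after day 5 as descriptive.
- If wanted, add a rank analysis with death in the window placed worst, as a sensitivity analysis.

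The common window deals with unequal monitoring length, and the division deals with truncation by death; both are needed. The cost is small: the daily hours are already recorded, monitored hours must be captured with them, and readings after day 5 leave the comparison. Treatment, length of monitoring and sample size do not change.

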### Statistical analysis

The analysis will be processed on the principle of intention. Patients who drop out or violate initial distribution will be considered as the worst outcome. Considering the probability of craniotomy patients treated by salvage DC, an as-treated analysis will also be implemented, as recommended in two-arm clinic trial [39]. Parametric data will be described by mean and standard deviation. Non-parametric data will be described by median and quartile. Categorical data will be presented using number and percentage.

The primary outcome of the study will be evaluated using the Pearson chi-square test with unadjusted risk ratio and 95 % confidence interval. Adjusted analysis of primary outcome will be assessed using logistic regression for pre-specified factors and any other covariates presenting significant difference between the two groups. The pre-specified subgroups include: age, GCS, pupillary response, mass lesion type and hypotension. Secondary outcome including assessment of quality of life, mortality at 6 and 12 months and incidence of complications will also be assessed using unadjusted analysis and adjusted regression. To investigate the risk factors of postoperative refractory hypertension (salvage DC), univariate and multivariate analysis will be used to identify potential variables of craniotomy patients.

Depending on the results of regression models, the receiver operating curves will be used to evaluate the discrimination. The Hosmer–Lemeshow test will process the goodness-of-fit of models [40]. A P value < 0.05 is considered statistically significant. All statistical analysis will be computed by SPSS software (version 19.0).

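### Total ICP and CPP burden are raw day counts with no allowance for days monitored or death during monitoring, so they mix pressure control with observation time

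*Protocol article*

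**What the plan says.** Under Outcomes, the further secondary endpoints include "ICP and CPP control and incidence of salvage DC in craniotomy patients". Follow-up and data collection gives two measures of post-operative ICP control: "daily ICP burden (number of hrs/d with ICP > 25 mmHg" and "total ICP burden (number of days with ICP" above 25 mmHg. CPP below 60 mmHg is handled alike: "as well as the same method recording daily and total CPP burden".

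Three other statements bear on the point:

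- Interventions says the monitor is "kept at least 5 days after surgery". This is a minimum with no stated end.
- Follow-up and data collection places ICP and CPP control at the 1-week assessment and adds "Patients who cannot be followed up at seven days will be assessed upon being discharged".
- Statistical analysis says "Patients who drop out or violate initial distribution will be considered as the worst outcome". That rule names neither death nor the end of monitoring.

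**The concern.** A count of days beyond a threshold can only grow while the patient is observed. Two patients with the same daily risk of raised ICP get different expected totals if one is monitored for 5 days and the other for 7. A patient who dies early with uncontrolled pressure can add only a few days and may score lower, which reads as better controlled, than a survivor with brief rises on more days.

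The arms differ in bone-flap management, which may affect ICP and so how long a probe stays in beyond day 5, and the treating team is not blinded. At stake is the comparison of one secondary measure: it could show a difference that reflects observation time, or hide or reverse one caused by early deaths.

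**Working it through.** The documents give no figure for ICP burden, so there is no stated result to reproduce. From the plan come the definitions, the 5-day minimum, the 1-week collection point and 168 patients per arm (Sample size). All rates below are assumptions.

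**Notation.** d = share of an arm dying early; m = days a dying patient is monitored; r = chance that such a day is raised (0.9); L = days a survivor is monitored; q = chance that a survivor's day is raised.

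- Expected raw count = (1 − d) × L × q + d × m × r
- Expected fraction of monitored days = (1 − d) × q + d × r

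**1. Single patients, no rates needed.** Patient A is raised throughout 2 days, then dies. Patient B is raised for 1 hour on each of 3 days and is monitored for 5 days. The raw totals are 2 and 3, so A ranks as better controlled. As hours over hours monitored, A has 48/48 = 100% and B has 3/120 = 2.5%.

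**2. Unequal monitoring, same risk.** Take d = 0.15 in both arms, m = 2 and q = 0.4.

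- L = 5: 0.85 × 2.0 + 0.15 × 1.8 = 1.97 days
- L = 7: 0.85 × 2.8 + 0.15 × 1.8 = 2.65 days
- False difference = 0.68 day. The fraction is 0.85 × 0.4 + 0.15 × 0.9 = 0.475 in both arms.

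The difference in general is 0.85 × q × (gap in days). For 5 versus 7 days it is 0.68, 0.51 and 0.34 day at q = 0.4, 0.3 and 0.2. For 6 versus 7 days it is 0.34, 0.26 and 0.17 day. In 4000 simulated trials with 168 per arm, the 5-versus-7 count was significant at the 5% level in 100%, 99% and 91% of trials. The 6-versus-7 count was significant in about 73%, 58% and 36%. The fraction rejected in about 5% throughout. Days were simulated as independent within a patient; clustering of raised days would widen the variance and lower the rejection rates for the count.

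**3. Unequal early death, same monitoring of survivors.** Take d = 0.10 versus 0.20. The count in the arm with fewer deaths minus that in the arm with more is 0.10 × (L × q − m × r). A positive value means the count favours the arm with more deaths.

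| L | q | m | Difference (days) |
|---|---|---|---|
| 7 | 0.4 | 1 | 0.10 × (2.8 − 0.9) = +0.19 |
| 7 | 0.4 | 2 | 0.10 × (2.8 − 1.8) = +0.10 |
| 5 | 0.4 | 2 | 0.10 × (2.0 − 1.8) = +0.02 |
| 7 | 0.4 | 3 | 0.10 × (2.8 − 2.7) = +0.01 |
| 7 | 0.2 | 2 | 0.10 × (1.4 − 1.8) = −0.04 |
| 5 | 0.4 | 3 | 0.10 × (2.0 − 2.7) = −0.07 |
| 7 | 0.4 | 4 | 0.10 × (2.8 − 3.6) = −0.08 |

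The sign turns where m × r = L × q, which for L = 7 and q = 0.4 is m = 2.8/0.9 = 3.1 days. In simulation, the +0.10 case was significant in about 11% of trials and the +0.19 case in about 24%. At q = 0.4 the fraction is 0.45 versus 0.50, so it shows the arm with more deaths as 5 points worse in every such row.

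**The case against.** **The endpoint has a second measure.** Daily burden, in hours per day, already separates one raised hour from a fully raised day. This stands. A reader might infer that the plan cannot tell those days apart, and the text does not support that. The companion measure does not, however, repair the total.

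**The 5-day minimum limits the problem.** Probe removal before day 5 in a survivor would depart from the protocol, and collection at 1 week suggests that survivors differ mainly over days 5 to 7, although no cut-off is stated. This also stands. Early death is not bounded by that minimum.

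**The largest figure needs an extreme case.** The 0.68 day requires every survivor in one arm to stop at day 5, every survivor in the other to reach day 7, and the daily risk to be unchanged on days 6 and 7. If probes come out because ICP is low, the unmonitored days would mostly add nothing, and the raw count would be close to the true 7-day count. Dividing by each patient's own monitored time would then overstate burden (2/5 = 40% against 2/7 = 29%). This is a fair criticism of a simple denominator, and the reason to use a common window.

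**Detail may sit elsewhere.** An analysis plan could add a denominator, and the article's list of secondary analyses does not name ICP burden. But the article itself states the definition of the total, so a plan that normalised it would have to override that text. Mortality is reported separately, so excess deaths would be visible beside the ICP results. That helps a reader but does not correct the measure.

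**Conclusion.** The point holds in limited form. As defined, total ICP and CPP burden mix pressure control with days monitored and with early death. A reader might go further and infer that the comparison will be biased, or will favour the arm with more deaths. The documents do not support that: they give no monitoring time, early mortality or daily risk by arm, and the sign changes with those values.

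Under the assumed values, early deaths shift the comparison from −0.08 day (correct direction) through near zero to +0.1 to +0.2 day in favour of the arm with more deaths, the last only when deaths come in the first day or two and daily risk is high. Unequal monitoring gives 0.17 to 0.68 day, the upper end being the extreme case. Daily burden is less exposed. The primary GOSE analysis, EQ-5D and the sample size are untouched. Severity is minor to moderate.

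**What to change.** Define total ICP burden as hours with ICP above 25 mmHg divided by hours monitored within a common window, the first 5 post-operative days that the protocol already requires. Define total CPP burden likewise for CPP below 60 mmHg. Report monitored hours by arm. Show patients who die within the window separately, or rank them worst in a sensitivity analysis. This changes the analysis definition only, not how patients are monitored.

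The cost is small. The hours for the numerator are already recorded for the daily burden; the denominator needs probe start and stop times on the CRF. The downside is that readings after day 5 leave this summary; they can still be described separately with the number of patients monitored on each day.
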